## Abstract

**Background:**

The growing population of cancer survivors faces persistent physical and emotional challenges that significantly impact health-related quality of life (HRQL). To address these multifaceted needs, robust and culturally adapted patient-reported outcome measures (PROMs), such as the Measure Yourself Concerns and Wellbeing (MYCaW) questionnaire, are essential for understanding and improving survivors’ subjective experiences.

**Objective:**

This protocol aimed to outline the systematic translation and cultural adaptation of the MYCaW questionnaire into German. The MYCaW questionnaire, a PROM, is designed to capture individualized concerns and assess overall well-being, particularly in cancer care settings. By adhering to common guidelines, this research will provide a tool for assessing individualized concerns and patient needs among German-speaking patients with cancer.

**Methods:**

Following International Society for Pharmacoeconomics and Outcomes Research (ISPOR) guidelines, this study will use a structured methodology involving forward and backward translation, expert review, patient review process, and preliminary validation to ensure linguistic and cultural equivalence. This study is approved by the ethics committee of the Medical Association Berlin (reference Eth-27/10). Construct validity will be assessed through comparison with the European Organisation for Research and Treatment of Cancer—Quality of Life Questionnaire, Core 30 (EORTC QLQ-C30) and the MIDOS (Minimal Documentation System; in German: Minimales Dokumentationssystem) questionnaire, to evaluate both quality of life and symptom burden.

**Results:**

Funding of the study was obtained in January 2023. Patient recruitment started in the first quarter of 2023, and the cognitive debriefing phase is ongoing. Validation with the larger patient sample (N=120) is scheduled to conclude in the fourth quarter of 2025, with publication of the study results anticipated in the first quarter of 2026. The adaptation process will include translation, expert review, and cognitive debriefing with patients and health care professionals to ensure linguistic clarity and cultural relevance.

**Conclusions:**

The translation and adaptation of MYCaW into German will contribute to expanding the availability of validated PROMs for German-speaking populations. By following rigorous international guidelines, this study aims to produce a reliable, culturally appropriate, and linguistically adapted German version of the MYCaW questionnaire for assessing patient concerns and well-being in oncology and supportive care settings. Future validation studies will be necessary to assess the psychometric properties of the adapted questionnaire and its applicability in clinical and research contexts. Potential challenges, such as maintaining conceptual equivalence in translation and ensuring broad representativeness in the validation process, will be addressed through iterative refinement. Once validated, the German MYCaW will provide a valuable resource for patient-centered research and care, helping to capture individualized concerns that might be overlooked by standardized instruments.

## Introduction

A growing number of people are living with cancer or have survived it, making the well-being of these individuals an important area for research [1]. In addition to the advances in early detection and the increasing efficacy of oncology therapies, understanding and improving the health-related quality of life (HRQL) of patients with cancer has gained increasing attention. Many patients with cancer face persistent physical and emotional challenges long after completing primary therapy. Long-term and late effects of cancer treatments—such as chronic pain, cognitive dysfunction, and severe fatigue—can significantly impact HRQL [2,3]. These impairments often necessitate comprehensive strategies to address the multifaceted needs of oncology patients.

The assessment of HRQL relies on validated patient-reported outcome measures (PROMs) [4]. These tools provide invaluable insights into patients’ subjective experiences, aiding clinicians and researchers in identifying specific areas requiring intervention [5]. One such tool, the Measure Yourself Concerns and Wellbeing (MYCaW) questionnaire, is recognized for its ability to capture individualized concerns and overall well-being [6]. MYCaW uses a patient-centered approach, allowing participants to report their primary concerns and assess their well-being, making it particularly useful in integrative oncology settings. The MYCaW questionnaire was first introduced in 2006 by Paterson et al [6] at the University of Bristol with support from the Medical Research Council Health Services Research Collaboration. Earlier work on MYCaW at the Bristol Cancer Help Center was recognized for its impact, earning a place on the shortlist and winning the Healthcare and Medical Research category at the 2003 Charity Awards. In 2020, Polley et al [7] and Seers et al [8] took over responsibility for MYCaW and Measure Yourself Medical Outcome Profile (MYMOP) leading to the foundation of Meaningful Measures Ltd [7-9] to manage the licensing of the questionnaire [10], while providing tailored guidance on capturing person-centered outcomes.

Most PROMs focus on predefined domains such as symptom burden, functioning, or general quality of life [4,11,12]. While these instruments are essential, they often fail to capture the individualized concerns that many patients identify as most pressing. In integrative oncology, where care extends beyond symptom control to include psychosocial and existential dimensions, such patient-defined concerns are particularly relevant [13,14]. Studies have shown that individualized priorities—such as fear of recurrence, family-related worries, or coping with identity changes—are frequently underrepresented in standardized PROMs [15]. Internationally, the MYCaW questionnaire has proven effective in addressing this gap and has been successfully adapted into several languages [16-20]. However, no validated German version currently exists. This represents a significant unmet need, as German-speaking oncology patients and researchers lack access to a culturally adapted tool for systematically documenting patient priorities and for enabling comparability across international studies.

The cross-cultural adaptation and validation of PROMs are essential to ensure their relevance and applicability across different languages and cultural contexts [21]. Translation is a critical first step in this process, requiring not only linguistic precision but also cultural sensitivity to maintain the questionnaire’s conceptual equivalence and reliability. To guide this process, the widely recognized framework by Beaton et al [21] outlines a systematic multistep methodology involving forward and backward translations, expert review, and patient review processes to ensure conceptual equivalence between the original and adapted versions. In addition, the International Society for Pharmacoeconomics and Outcomes Research (ISPOR) principles for good practices in translation and cultural adaptation emphasize maintaining linguistic precision and cultural sensitivity [22], while the Consensus-based Standards for the selection of health status Measurement Instruments (COSMIN) guidelines provide recommendations for assessing the measurement properties of translated instruments [23], such as validity, reliability, and cross-cultural equivalence. Together, these frameworks ensure that adapted tools are both culturally relevant and psychometrically sound.

This study protocol outlines the process of translating the MYCaW questionnaire into German and aims to provide a detailed framework for its cultural adaptation. By achieving a validated German version, this research aims to facilitate its use among German-speaking patients with cancer, enabling a deeper understanding of their self-reported individualized concerns and needs.

The primary objective of this protocol is to describe the methodology used in the translation and adaptation of the MYCaW questionnaire into German. Ultimately, the study aims to contribute to the broader field of patient-centered oncology care by enabling more accurate and culturally appropriate assessments of HRQL in German-speaking settings.

## Methods

### Study Design

This study will follow the ISPOR guidelines for the translation and cultural adaptation of patient-reported outcome measures [22] and the COSMIN guidelines for assessing cross-cultural validity and measurement invariance [23]. The process includes preparation, translation, patient review, and validation. The study protocol was written using the SPIRIT (Standard Protocol Items: Recommendations for Interventional Trials) reporting guidelines [24].

### Study Setting

This study is conducted by the Research Institute Havelhöhe (Forschungsinstitut Havelhöhe) at the hospital Gemeinschaftskrankenhaus Havelhöhe in Berlin within the Network Oncology [25].

### Ethical Considerations

This study adheres to the principles of the Declaration of Helsinki and has received approval from the Ethics Committee of the Berlin Medical Association (Ethik-Kommission der Ärztekammer Berlin) under reference Eth-27/10. This trial is registered in the German Clinical Trials Register (DRKS00013335; registered on November 27, 2017). Written informed consent will be obtained from all participants before enrollment. Any significant protocol deviations or modifications will be reported to the Ethics Committee and the German Clinical Trials Register. A completed SPIRIT 2013 checklist is provided (see Checklist 1). Patients and the public were not involved in the design, reporting, or dissemination plans of the study protocol of this research but will be involved in the conduct of the outlined study in the future during the debriefing and validation process. All participants receive written and verbal information about the study, including its purpose, procedures, risks, and benefits, and will give written informed consent before participation. They may withdraw at any time without consequences. Participant privacy and confidentiality will be strictly protected. Identifiable information will be stored separately from research data on secure, password-protected institutional servers accessible only to authorized study personnel. Data will be pseudonymized for analysis, publication, and possible sharing and retained only as long as legally and scientifically required. Participation involves minimal risk and no invasive procedures. No financial incentives are offered. This protocol complies with JMIR’s ethical reporting guidance

### Translation Process

Figure 1 shows the flowchart illustrating the systematic process of the questionnaire translation into German language following the ISPOR guidelines. The steps ensure linguistic and conceptual equivalence between the original and translated versions, maintaining validity and reliability. The translation process involves 2 independent bilingual translators (native German speakers fluent in English) who will produce 2 German versions of the MYCaW questionnaire. These versions will be, after discussion of discrepancies, combined into a single German draft (see Figure 1).

The translators will focus on maintaining conceptual equivalence rather than literal translation, considering cultural nuances and medical terminology.

This process is followed by 2 back-translations into English with the help of 2 native independent English speakers fluent in German. The backward translations will be compared with the original MYCaW questionnaire to identify discrepancies (see Figure 1). A reconciliation meeting including translators and a third bilingual expert will be held to resolve semantic, idiomatic, and conceptual discrepancies, ensuring conceptual equivalence. A panel of experts, including oncologists, psychologists, and patient representatives, will review all versions to ensure linguistic and cultural accuracy. The panel will finalize a pretest version of the German MYCaW questionnaire.

**Figure 1. F1:**
[figure not shown]
Flow chart of the translation process according to International Society for Pharmacoeconomics and Outcomes Research (ISPOR) guidelines. MYCaW: Measure Yourself Concerns and Wellbeing.

### Participant Review

A total of 15 patients with cancer will be recruited for cognitive debriefing based on diversity in age, cancer type and stage, treatment history, and educational background. This purposive sampling approach is intended to enhance representativeness within the single-site setting and to capture a broad spectrum of patient perspectives. Inclusion criteria are providing written informed consent, being 18 years and/or older, having a confirmed (any) cancer diagnosis, and having sufficient German language proficiency. Exclusion criteria are no written informed consent and cognitive impairment of the patient. The pretest version will be evaluated by these patients for its clarity, cultural relevance, and ease of understanding. Semistructured interviews will be conducted to gather participants’ feedback on specific items (see Figure 1).

### Analysis of Cognitive Debriefing Interviews

Cognitive debriefing interviews will be audio-recorded, transcribed verbatim, and analyzed using qualitative content analysis according to Mayring [26]. In addition, 2 researchers will independently code the transcripts, combining deductive categories (eg, clarity, cultural relevance, and comprehensibility) with inductive categories emerging from the data. Discrepancies will be resolved by discussion or with a third reviewer. Findings will be summarized in matrices to identify key issues and inform refinement of the German MYCaW version.

### Validation Phase and Psychometric Testing

The subsequent validation phase will include approximately 120 participants from the same site, but purposive sampling will again be applied to ensure heterogeneity in demographic and clinical characteristics. This sample aligns with COSMIN recommendations for studies assessing psychometric properties. Specifically, it meets thresholds considered “very good” for evaluating internal consistency and construct validity and provides sufficient power for exploratory analyses of structural validity and reliability. Content validity will be assessed through patient feedback, which helps ensure that the questionnaire items are relevant, comprehensive, and representative of the real experiences of the patients with cancer. This will involve qualitative methods such as interviews or surveys to compare MYCaW content with participant-reported concerns and well-being issues. Internal consistency will be evaluated using Cronbach α, with a commonly accepted threshold for good internal consistency of 0.7 or higher [27]. This will be calculated for each subscale of the MYCaW questionnaire to ensure that items within each dimension of HRQL are consistent and reliable in measuring the same underlying construct. To ensure consistency and reliability in the qualitative analysis of patient concerns, all coders will undergo structured training in the use of the adapted MYCaW coding framework. This training will include familiarization with category definitions, practice sessions using sample data, and calibration exercises to align interpretation. Coding discrepancies between raters will be addressed through a consensus process involving joint review and discussion. If no consensus can be reached, a third independent expert will be consulted to resolve the disagreement.

To assess construct validity, the MYCaW questionnaire that will be compared with the EORTC-QLQ C30 is the European Organisation for Research and Treatment of Cancer—Quality of Life Questionnaire, Core 30 (EORTC-QLQ C30) [11], and the MIDOS questionnaire [28] for HRQL measures will be used to examine whether the MYCaW questionnaire captures similar constructs and whether changes in MYCaW scores align with changes in other established measures. This approach helps to ensure that the MYCaW questionnaire is measuring HRQL in a manner consistent with these validated tools. While the EORTC-QLQ C30 evaluates HRQL across multiple domains (symptom scales and functioning scales), the MIDOS assesses symptom burden in palliative or supportive care contexts. This dual comparison allows analysis of both standardized and patient-prioritized concerns.

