### Timeline and Milestone Plan of the Study

Table 1 presents the timeline of the MYCaW translation and validation process. Key milestones and projected completion dates are highlighted, with further details available in Figure 2 (Gantt chart). The finalized German version will undergo preliminary testing with a larger sample to assess reliability and validity (see Table 1). The psychometric properties to be evaluated include content validity, internal consistency, and construct validity. These psychometric evaluations are critical to ensuring that the translated MYCaW questionnaire is both reliable and valid for assessing HRQL among German-speaking oncology patients.

Figure 2 presents the Gantt chart outlining the timeline of the MYCaW translation process. Key milestones and projected completion dates are highlighted, with further details available in Table 1.

**Table 1. T1:** Timeline of the study.

Phase and timeline	Translation process
Year 2023: Translation process completion (Phase 1)	
Quarter 4, 2023 to Quarter 2, 2024	Finalize the German MYCaW^a^ version after translation, reconciliation, and expert review.
Year 2024: Patient review process and preliminary validation (Phase 2‐3)	
Quarter 2, 2024 to Quarter 3, 2024	Patient review process. Test the prefinal version with 15 patients, conduct interviews, and refine based on feedback.
Quarter 3, 2024 to Quarter 4, 2024^b^	Finalize the German version, begin validation with a larger sample (N=120) of participants, and assess psychometric properties (content validity, internal consistency, and construct validity).
Year 2025: Data analysis, final testing, and study conclusion (Phase 4‐6)	
Quarter 4, 2024 to Quarter 3, 2025	Continue validation and finalize data collection. Complete recruitment, conduct final psychometric analysis, and review preliminary results.
Quarter 3, 2025 to Quarter 4, 2025	Conclude study and finalize participant follow-up. Publish findings, present results, and complete study.
December 2025: Study officially ends.	

a MYCaW: Measure Yourself Concerns and Wellbeing.

b Contingency planning allows for time extensions in quarter 3–quarter 4, 2024, to allow for potential recruitment delays.

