## Discussion

### Principal Findings

This study outlines a systematic approach to the translation and cultural adaptation of the MYCaW questionnaire into German, which is essential for capturing individualized patient concerns in integrative oncology. MYCaW has been widely used in various research settings to assess patient-reported concerns and overall well-being. Its flexible and patient-centered design allows individuals to express their most pressing issues, making it particularly suitable for integrative oncology and supportive care [6]. Across health care contexts, MYCaW has shown value in complementing standardized HRQL tools.

Several studies have used MYCaW to explore the impact of interventions, assess patient priorities, and track changes in well-being over time [6,20,29,30]. Previous research demonstrated that MYCaW captures nuanced, patient-specific concerns that standardized questionnaires may overlook, thereby facilitating tailored interventions that may improve overall quality of life [6,8]. For example, in a palliative care setting, MYCaW’s open-ended design provided valuable qualitative insights into patient needs, and health care professionals reported it as easy to use and beneficial for patient-focused discussions [29]. A standardized coding framework with 5 super-categories and 36 specific categories was developed to analyze concerns, achieving high interrater reliability (κ=0.905) [29]. In addition, studies comparing MYCaW with established HRQL measures, such as the EORTC QLQ-C30, also found it complements existing tools by offering a more individualized assessment [30].

Like MYCaW, the precursor questionnaire MYMOP has also been used extensively to evaluate patient-centered outcomes. While MYMOP focuses on symptom-specific concerns and treatment effects, both instruments share a common philosophy of prioritizing patient voice and individualized health concerns [31]. MYCaW is particularly relevant in psycho-oncology due to its focus on well-being.

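### Cronbach α for each MYCaW subscale does not fit an instrument in which each patient names their own concerns, and cannot show how reliably those concerns are scored

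*Protocol article*

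**What the plan says.** The protocol article, under Validation Phase and Psychometric Testing, states: "Internal consistency will be evaluated using Cronbach α, with a commonly accepted threshold for good internal consistency of 0.7 or higher". It then fixes the unit of calculation: "This will be calculated for each subscale of the MYCaW questionnaire to ensure that items within each dimension of HRQL are consistent and reliable". The consistency it has in mind is that of items "in measuring the same underlying construct". That is a measurement model in which fixed items are grouped into subscales and each subscale reflects one construct.

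The instrument is described differently elsewhere. In the Introduction, "MYCaW uses a patient-centered approach, allowing participants to report their primary concerns and assess their well-being". The Introduction also justifies MYCaW by contrast: "Most PROMs focus on predefined domains such as symptom burden, functioning, or general quality of life", and such instruments are said to miss individual priorities such as fear of recurrence or family worries. Principal Findings adds: "Its flexible and patient-centered design allows individuals to express their most pressing issues", and calls the format open-ended.

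Timeline and Milestone Plan of the Study says: "The psychometric properties to be evaluated include content validity, internal consistency, and construct validity". Table 1 repeats these three. The same section calls the evaluations critical to the translation being reliable as well as valid. The Results section separately plans an interrater reliability assessment for the coding of concerns.

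**The concern.** Cronbach α presupposes that all respondents answer the same items and that those items reflect one construct. Where patients name their own concerns, the same slot on the form may hold fear of recurrence for one patient and a family worry for another. Two concerns of the same patient need not share a construct. The article names no subscale or dimension to which the α sentence could apply. A rating that stands alone has no α at all.

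This matters because, of the three listed properties, only internal consistency bears on the reliability of patients' scores. Applied to the concern ratings, α could make the German version look unreliable because patients named different problems. It could equally make it look reliable because distressed patients rate everything as severe.

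**Working it through.** **Inputs from the article.** α with benchmark 0.7, per subscale, and about 120 participants in validation. The 0.7 is a cited convention. The 120 is supported by a COSMIN category, without an expected α, item count or precision, so there is no calculation to reproduce.

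**Assumptions, not in the article.** Each named concern carries a severity rating, and k = 2 or 3 ratings are combined (k = 4 and 6 are shown for range). In the simulation, each rating has a retest reliability of 0.90.

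**Step 1: what α = 0.70 requires.** Standardised α = k·r / (1 + (k − 1)·r), where r is the mean correlation between ratings. Solved for α = 0.70, r = 0.7 / (k − 0.7·(k − 1)).

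- k = 2: 0.7 / 1.3 = 0.538
- k = 3: 0.7 / 1.6 = 0.4375

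| k | r needed | α at r = 0.1 | 0.2 | 0.3 | 0.4 | 0.5 | 0.6 |
|---|---|---|---|---|---|---|---|
| 2 | 0.54 | 0.18 | 0.33 | 0.46 | 0.57 | 0.67 | 0.75 |
| 3 | 0.44 | 0.25 | 0.43 | 0.56 | 0.67 | 0.75 | 0.82 |
| 4 | 0.37 | 0.31 | 0.50 | 0.63 | 0.73 | 0.80 | 0.86 |
| 6 | 0.28 | 0.40 | 0.60 | 0.72 | 0.80 | 0.86 | 0.90 |

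The article gives no value of r, so no row or column is the expected one.

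**Step 2: does α track reproducibility?** Simulation with n = 120, 2,000 runs per scenario and rating reliability held at 0.90. Only ρ, the correlation between the true severities of a patient's concerns, changes.

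| ρ | k = 2: mean α | P(α ≥ 0.7) | retest correlation of sum | k = 3: mean α | P(α ≥ 0.7) | retest correlation of sum |
|---|---|---|---|---|---|---|
| 0 | −0.02 | 0.000 | 0.90 | −0.01 | 0.000 | 0.90 |
| 0.3 | 0.41 | 0.000 | 0.92 | 0.52 | 0.002 | 0.93 |
| 0.5 | 0.61 | 0.106 | 0.93 | 0.71 | 0.582 | 0.95 |
| 0.6 | 0.70 | 0.519 | 0.93 | 0.78 | 0.974 | 0.95 |
| 0.8 | 0.83 | 0.998 | 0.94 | 0.88 | 1.000 | 0.96 |

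A check by formula at ρ = 0.3, k = 2: the observed correlation is 0.9 × 0.3 = 0.27, so α = 0.54 / 1.27 = 0.43 (simulated mean 0.41). The retest reliability of the sum is 0.9 × 1.3 / (0.9 × 1.3 + 0.1) = 1.17 / 1.27 = 0.92.

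Across the scenarios, retest reliability stays between 0.90 and 0.96, while α runs from about 0 to 0.83 (k = 2) or 0.88 (k = 3). What moves α is how far a patient's concerns rise and fall together.

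**The case against.** The strongest reply is that the article does not give MYCaW's scored items. It states no number of concerns, no rating scale and no rule for summing. The well-being assessment is put to every patient, and the full protocol may define a set of common items for which α is sound. This stands, and it limits the point: α is not wrong in itself, and deleting it outright would go too far. It does not rescue α for the concern ratings, because the mismatch lies between two things the article does state.

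Several stronger readings are tempting, and the article does not support them.

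- *A well-adapted questionnaire would be expected to fail.* That follows only if r lies below the break-even value. A range of 0.1 to 0.4 lies wholly below 0.54 and 0.44, so it builds failure in, and the article gives no correlations.
- *The 0.7 is a pass/fail rule.* It is cited as a common benchmark. No section says the German version is rejected or revised below it.
- *α is the only reliability analysis.* Interrater reliability and exploratory reliability analyses are also mentioned. That they carry no statistic or cut-off may be a matter of condensation, and the absence of a retest plan is not the point made here.

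It may also be said that α is a lower bound for the reliability of a sum. That requires uncorrelated errors, which ratings made at one sitting under the same distress do not guarantee. No summed score is described either.

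Finally, the article calls this testing preliminary and defers larger validation to later studies. That lowers the stakes but does not make the statistic fit.

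**Conclusion.** The point holds in limited form. The plan fixes a statistic per subscale and per dimension, while the article describes no subscale and presents an instrument built on concerns that each patient names. For ratings of those concerns, α reflects how they vary together. With an assumed 2 or 3 ratings, it reaches 0.70 only when the mean correlation is at least 0.54 or 0.44. A value on either side of the benchmark would not inform about measurement error in the German version, yet internal consistency is the only listed property that addresses score reliability.

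The break-even values depend on the assumed number of ratings, and the simulation also on the assumed rating reliability of 0.90. The mismatch itself depends on neither. Whether α would in fact fall above or below 0.7 cannot be said from the article.

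**What to change.** - State which MYCaW items are scored. Do not apply α or the 0.7 benchmark to patient-nominated concern ratings. Keep α only for a set of fixed items common to all patients, if one exists. Treat each concern rating and the well-being rating as a single-item score.
- Report the interrater reliability already planned in the Results section as κ with a 95% CI, computed on the coders' independent codes before consensus. Label it as coding reliability only, since it measures agreement between coders and not error in patients' scores.
- The validation section intends to compare changes in MYCaW scores with changes in other measures, which implies a repeat administration. If it takes place, report an ICC with a 95% CI in patients judged stable, with stability defined beforehand. Stability on the EORTC QLQ-C30 alone would be a weak definition, because the Introduction says individual concerns are underrepresented in standardised questionnaires.
- If there is no repeat administration, take the word reliable out of the score-level conclusion in Timeline and Milestone Plan of the Study.

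The cost is chiefly wording, with no additional patients. The study gives up a familiar statistic for the concern ratings and may have to make a narrower reliability claim.
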